### Efficacy

The goal of this study is to assess the preliminary efficacy and safety of surfactant administration, identify an efficacy signal quickly (if present) to consider initiation of a larger randomised controlled clinical trial, and assess the potential impact of total dose on preliminary efficacy.

The change in PaO2/FiO2 ratio relative to baseline at 24 hours after the last dose of surfactant and the change in Ventilation Index relative to baseline at 24 hours after the last dose of surfactant will be analysed separately. For each endpoint, a test for a total dose-response effect using a model-based multiple contrast test (Bretz et al, 2005) will be performed. Candidate dose-response models will include linear and Emax. The change in PaO2/FiO2 and change in Ventilation Index may be transformed for analysis (e.g., log transformed) to better satisfy normality assumptions of model residuals. The primary analysis will be done on patients with observed data at 24 hours ("completers"), though sensitivity analyses will also be performed if data are missing at 24 hours in an informative manner (e.g., due to death) where a non-parametric approach can accommodate missing data by assigning the worst rank.

The table below shows the power to show a significant dose response under varying assumed true dose response curves when using 12 matched controls.

| CV                                      | Relative change from baseline, on average |                           |                           |                           |                           | Power to show dose response |
|-----------------------------------------|-------------------------------------------|---------------------------|---------------------------|---------------------------|---------------------------|-----------------------------|
|                                         | Control                                   | Cohort 1 (30 total vials) | Cohort 2 (50 total vials) | Cohort 3 (70 total vials) | Cohort 4 (90 total vials) |                             |
| 20%                                     | 0%                                        | 0%                        | 0%                        | 0%                        | 0%                        | 0.05                        |
|                                         | 0%                                        | 10%                       | 20%                       | 30%                       | 40%                       | 0.89                        |
|                                         | 0%                                        | 25%                       | 25%                       | 25%                       | 25%                       | 0.82                        |
|                                         | 0%                                        | 0%                        | 25%                       | 25%                       | 25%                       | 0.75                        |
|                                         | 0%                                        | 0%                        | 0%                        | 30%                       | 30%                       | 0.72                        |
|                                         | 0%                                        | 0%                        | 0%                        | 0%                        | 50%                       | 0.63                        |
| 25%                                     | 0%                                        | 0%                        | 0%                        | 0%                        | 0%                        | 0.05                        |
|                                         | 0%                                        | 10%                       | 20%                       | 30%                       | 40%                       | 0.77                        |
|                                         | 0%                                        | 25%                       | 25%                       | 25%                       | 25%                       | 0.66                        |
|                                         | 0%                                        | 0%                        | 25%                       | 25%                       | 25%                       | 0.57                        |
|                                         | 0%                                        | 0%                        | 0%                        | 30%                       | 30%                       | 0.54                        |
|                                         | 0%                                        | 0%                        | 0%                        | 0%                        | 50%                       | 0.49                        |
| Based on 2000 simulations for each row. |                                           |                           |                           |                           |                           |                             |

When the true residual CV is 20%, there is reasonable power to detect a dose response for either endpoint when the true increase is at least 20-30% in two or more cohorts. There is limited power to detect a dose response when the effect is only in the highest cohort. Also, when the true residual CV is larger, the power reduces substantially. To reduce residual variability, the fitted model will also adjust for the baseline  $\text{PaO}_2/\text{FiO}_2$  ratio or Ventilation Index as a proxy measure of baseline severity. Significant dose response model fits can be utilized to estimate doses that provide clinically meaningful results and aid in planning for future studies.

Efficacy data will be continuously reviewed after each cohort to assess whether results are compelling enough to suggest initiation of a larger randomised controlled clinical trial. Interim efficacy data will be analysed using a simple Bayesian adaptive approach. After each cohort completes dosing plus 24 hours of follow-up, the posterior distributions of the mean change in  $\text{PaO}_2/\text{FiO}_2$  ratio and the mean change in Ventilation Index will be determined under an assumed normal distribution with a non-informative prior. The change in  $\text{PaO}_2/\text{FiO}_2$  and change in Ventilation Index and may be transformed for analysis (e.g., log transformed) to better satisfy normality assumptions. Interim efficacy will be declared for the purposes of further trial planning if there is relatively high posterior probability (e.g., > 80%) that EITHER the true mean change in  $\text{PaO}_2/\text{FiO}_2$  OR mean change in Ventilation Index at 24 hours after last administration of surfactant “high” (e.g.,  $\geq 20\%$ ), either for an individual cohort or for all treated patients combined.

The following table shows the probability of observing at least 80% posterior probability that the true improvement is  $\geq 20\%$  on average for each endpoint.

|                                       |                                                                                                                 |
|---------------------------------------|-----------------------------------------------------------------------------------------------------------------|
| Relative change from baseline in each | Cumulative probability to observe at least 80% posterior probability that true change is $\geq 20\%$ on average |
|---------------------------------------|-----------------------------------------------------------------------------------------------------------------|

| group, on average                               | After 6 complete | After 9 complete | After 12 complete |
|-------------------------------------------------|------------------|------------------|-------------------|
| 0%                                              | 0.01             | 0.02             | 0.03              |
| 10%                                             | 0.06             | 0.14             | 0.19              |
| 20%                                             | 0.30             | 0.46             | 0.58              |
| 25%                                             | 0.45             | 0.64             | 0.75              |
| 30%                                             | 0.60             | 0.81             | 0.90              |
| 1000 simulations per row, assumes true CV = 20% |                  |                  |                   |

When there is no true improvement, there is < 5% probability to declare efficacy at an interim time point. When the true improvement is 30% on average, there is 60% (81%) probability to declare efficacy at an interim time point after 6 (9) patients complete the study.

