### 3.3 Outcome measures/endpoints

#### 3.3.1 Primary Endpoint

The co-primary endpoints are:

1. Change in  $\text{PaO}_2/\text{FiO}_2$  ratio 48 hours after study initiation
2. Change in the Ventilation Index 48 hours after study initiation

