#### 4 TRIAL DESIGN

This study is an exploratory, dose-escalating pilot trial to test the feasibility, safety and preliminary efficacy of aerosolized lung delivery of surfactant, a medicine with a known safety profile, to improve the oxygenation and pulmonary compliance of adult patients diagnosed with moderate to severe COVID-19 associated lung injury with increasing oxygenation requirements.

The timing of escalating dosing and assessment of clinical response is based on the rapid oxygenation response of infants with surfactant deficiency ([Collaborative European Multicenter Study Group 1988](#)) and the clinical response described in adults after endobronchial administration of surfactant in ARDS ([Walmrath 2002](#)). Nevertheless, it is acknowledged that the optimal dose required for surfactant replacement therapy in adults and the rate of clinical response in patients with COVID-19 are unknown. Therefore, we propose a dose-escalating, adaptive trial design in which the feasibility of administration of aerosolized surfactant and the clinical response in mechanically ventilated COVID-19 patients are assessed. The dosing regimen may be adjusted based on accumulating data and may depend on the dose required to achieve a clinical response and the speed with which that response is seen.

Patients will enter the study and will be randomised to 3:2 for the treatment and control arms where they will receive three doses of Alveofact® via nebulizer or the control arm where treatment will follow standard of care.

Patients in the treatment arm will be assigned into cohorts sequentially as follows:

- **COHORT 1:** 3 patients will receive 10 vials (1080 mg) each of Alveofact® at dosing times of 0 hours, 8 hours and 24 hours. 2 controls.

- **COHORT 2:** 3 patients will receive 10 vials (1080 mg) of Alveofact® at dosing times of 0 hours and 8 hours, and 30 vials (3240 mg) of Alveofact® at a dosing time of 24 hours. 2 controls
- **COHORT 3:** 3 patients will receive 10 vials (1080 mg) of Alveofact® at a dosing time of 0 hours, and 30 vials (3240 mg) of Alveofact® at dosing times of 8 hours and 24 hours. 2 controls
- **COHORT 4:** 3 patients will receive 30 (3240 mg) vials each of Alveofact® at dosing times of 0 hours, 8 hours and 24 hours. 2 controls

Control arm:

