## 8.7 Dosage schedules

Sequential vials of 108 mg Alveofact® in 2.2 mL buffer will be administered by nebulizer at 5-minute intervals with observation of vital signs, changes in oxygen saturation, FiO2 and Mean Airway Pressure. After each administration, 2 drops of normal saline will be nebulized, and the next vial administered. After administration of the first dose, dosing of Alveofact® will pause and vital signs and ventilation parameters will be assessed over the next 8 hours. If no grade 3 or grade 4 adverse events attributable to surfactant administration occur, another dose of Alveofact® will be administered and vital signs and ventilation parameters will be assessed over the next 16 hours. Again, if no grade 3 or grade 4 adverse events attributable to surfactant administration occur; a final dose of Alveofact® will be administered.

The dosing schedule for each group is displayed in the table below.

| Group | 0 Hours           | 8 Hours           | 24 Hours          |
|-------|-------------------|-------------------|-------------------|
| 1     | 10 x 108 mg vials | 10 x 108 mg vials | 10 x 108 mg vials |
| 2     | 10 x 108 mg vials | 10 x 108 mg vials | 30 x 108 mg vials |
| 3     | 10 x 108 mg vials | 30 x 108 mg vials | 30 x 108 mg vials |
| 4     | 30 x 108 mg vials | 30 x 108 mg vials | 30 x 108 mg vials |

If a dose time point is missed it should be administered as soon as it is possible. The investigator or delegate will assess the clinical stability of the patient prior to administering the dose or following a time point being missed or treatment being suspended.

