## 8.7 Dosage modifications

In an event when the administration of 30 vials is not practical, doses may drop to 20 or 10 vials, depending on feasibility. In the event clear efficacy is observed in cohort 1, doses may drop below 10 vials or dosing times may be reduced.

Progression and dosing modifications of subsequent cohorts will be decided by teleconference of the trial steering committee. Any safety concerns would be referred to the independent DSMB on completion of dosing of each cohort of 3 patients + 24 hours to enable collection of physiological outcomes.

The DSMB will actively monitor emerging safety and efficacy data to make recommendations about early study closure or the initiation of a larger randomised controlled clinical trial.

The dose administered cannot be modified due to patient / personal legal representative request.

Given the severity of the illness in ventilated Covid-19 patients, safety data will be interpreted with caution and will not be formally compared between active intervention and control groups.

- Dosing will be stopped in individual patients upon persistent deterioration of oxygenation during or after surfactant administration
- Study stopping rules for futility or efficacy are provided in the statistical analysis section.
- The protocol team will review emerging AE/SAE/SADEs data daily. If 3 or more patients develop the same SAE after administration of study drug, the study will be paused pending review by the DSMB. The study may also pause at the discretion of the Principal Investigator if there are a significant number of unexpected AEs/SAEs/SADEs and referred to the DSMB for review.
- The DSMB will formally review the safety data after every three subjects and is available for ad hoc reviews for other safety concerns as noted above.

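### Section 10 reads the co-primary endpoints 24 hours after the last surfactant dose, not at the defined 48 hours after initiation; the clocks part when dosing departs from schedule, and controls have no last dose

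*Protocol*

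**What the plan says.** The endpoint sections agree with one another. The trial summary and Sections 3.1, 3.3.1 and 3.4 place both co-primary endpoints at 48 hours; Section 3.3.1 words the second as "Change in the Ventilation Index 48 hours after study initiation". Sections 4 and 12 use the same 48-hour values for the escalation review and for source data verification.

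Section 10 (Efficacy) uses another clock. It states that "the change in Ventilation Index relative to baseline at 24 hours after the last dose of surfactant will be analysed separately", with PaO2/FiO2 timed alike. The interim posterior is calculated "After each cohort completes dosing plus 24 hours of follow-up", and the interim criterion again refers to 24 hours after the last administration. On the analysis set, "The primary analysis will be done on patients with observed data at 24 hours", with no origin given for those 24 hours. For informative missingness such as death, a sensitivity analysis is planned in which "a non-parametric approach can accommodate missing data by assigning the worst rank".

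Dosing is planned "at dosing times of 0 hours, 8 hours and 24 hours". Section 8.7 makes the second and third doses conditional on there being no attributable grade 3 or 4 adverse event, and adds two further rules: "Dosing will be stopped in individual patients upon persistent deterioration of oxygenation during or after surfactant administration" and "If a dose time point is missed it should be administered as soon as it is possible".

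**The concern.** A primary analysis should read every patient at the time at which the endpoint is defined, on a clock that both arms share. A clock that starts at the last dose depends on how treatment went. Patients whose dosing is cut short are read earlier than the rest, and two of the reasons for cutting it short (worsening oxygenation, attributable toxicity) are linked to the quantities being measured. Controls receive no surfactant, so the zero-dose anchor of the dose-response model has no stated reading time. With 3 treated patients per cohort, one shifted reading is a third of that cohort's data. A SAP written from this protocol would have to contradict either Section 3 or Section 10.

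**Working it through.** **Inputs.** Endpoint time: 48 h after initiation (3.3.1). Analysis time: last dose + 24 h (10). Planned dose times: 0, 8 and 24 h (4, 8.7). Treated patients per cohort: 3 (4).

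**Reading time under Section 10** = hour of last dose + 24.

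| Dosing actually given | Section 10 reading | Difference from 48 h |
|---|---|---|
| Dose 1 only | 0 + 24 = 24 h | 24 h early |
| Doses 1 and 2 | 8 + 24 = 32 h | 16 h early |
| All three, on time | 24 + 24 = 48 h | none |
| Dose 3 late by d hours | 24 + d + 24 = 48 + d h | d hours late |
| Control | no last dose | undefined |

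In the first row, the primary reading falls at the same hour as the separate 24-hour secondary endpoint of Section 3.3.2.

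**Start or end of the dose.** Section 10 does not say which. A 30-vial dose is 30 × 2.2 mL = 66 mL. At the stated maximum of 0.3 mL/min it takes 66/0.3 = 220 min = 3.7 h, so counting from its end puts even an on-schedule reading at about 24 + 3.7 + 24 = 52 h.

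**Leverage of one patient.** If one of three patients is read early, and the change from baseline at that time differs by D points from the value at 48 h, the cohort mean moves by D/3. The linear scenario in the power table has steps of 10 points between cohorts (10, 20, 30, 40%). One patient would need D = 3 × 10 = 30 points to move a cohort mean by one step. The documents do not say how likely that is.

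**Controls.** Section 4 mentions an equivalent time for controls, but only for the pause before cohort review. Sections 3.4 and 7.11 match control times for sampling and for the choline infusion. None of this is carried into Section 10.

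**The plan's own figures.** A simulation of the multiple contrast test (one-sided 5%, log scale, 12 controls, 3 treated per cohort, assumed ED50 of 10 vials) reproduces all 12 rows of the power table within 0.02; for example, at a CV of 20% the linear shape gives 0.90 against the stated 0.89. The interim table is also reproduced within 0.02. Neither calculation has time as an input, so neither is evidence on this point and neither changes with the fix. That the power table assumes 12 controls while the design has 8 is a separate matter.

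**The case against.** The best defence is that the planned times are identical. Every cohort has its third dose scheduled at 24 hours, so on schedule both clocks read 48 hours, and Sections 4 and 12 show that 48 hours is what the investigators have in mind. That stands, and it limits the problem to stopped, withheld, late or rescheduled dosing. The intent to match controls in time is also fairly clear from Section 4, and the interim rule concerns treated patients only, so the control gap matters mainly for the final dose-response test.

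Several stronger readings are tempting but not supported:

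- **That completers are judged before the third dose.** Read literally, data at 24 hours would mean a time when cohorts 1 and 2 have each had 20 vials. But the phrase follows two references to 24 hours after the last dose in the same paragraph and is most naturally shorthand for them. The wording is loose; it does not set a reading before the third dose.
- **That extubated survivors are scored like deaths.** Ventilation Index cannot be calculated without ventilator pressures, so such patients would drop out of the completer set. But the worst-rank rule gives only death as its example and says nothing about extubation, and no extubation rate is given.
- **That readings drift to 55 to 59 hours.** This needs nebuliser rates of 0.15 to 0.10 mL/min, derived from assumed breathing ratios. The protocol gives only the maximum rate.
- **That every early reading belongs to a deteriorating patient.** Section 8.7 also allows dosing times to be reduced after clear efficacy in cohort 1, which could give early readings in good responders. The direction of any bias is therefore not fixed.

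**Conclusion.** Section 10 contradicts the protocol's own definition of both co-primary endpoints, and leaves the control reading time unstated. It should be fixed. It is not a fatal flaw, because this is an exploratory pilot in which the two clocks coincide when dosing runs to plan.

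The size is known for the clock and unknown for the bias. Treated patients can be read 24 or 16 hours early, or late by the delay in the third dose. How far this distorts the dose-response test depends on how often dosing departs from schedule and on how much the measures change between the actual reading and 48 hours; the documents give neither. The conclusion assumes only that the stopping, withholding and late-dosing provisions of Section 8.7 will sometimes be used.

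**What to change.** In the main, interim and completer text of Section 10, replace the last-dose clock and the bare 24 hours with 48 hours after time zero. Define time zero as the start of dose 1, or the matched time for controls, and apply it whatever doses were given. Analyse patients by assigned cohort. Bring the data-collection wording in Section 8.7 (Dosage modifications), which allows each cohort 24 hours after completion of dosing, into line.

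Keep the planned contrast test in completers and the worst-rank sensitivity analysis for deaths. State in the latter that patients alive and extubated before 48 hours are not given the worst rank.

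The cost is wording and one check on data capture. Scheduled arterial gases end at 36 hours (Section 7.7 and Appendix 1). The list of parameters recorded to 48 hours in Section 7.7 includes PaO2, FiO2 and PEEP but not PaCO2, peak pressure or respiratory rate, all of which Ventilation Index needs. Confirm that a gas with PaCO2 and these ventilator values is captured at 48 hours. The present wording needs the same 48-hour reading whenever dosing is on schedule, so the fix does not create this requirement.

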### 6.2 Exclusion criteria

1. Imminent expected death within 24 hours
2. Specific contraindications to surfactant administration (e.g. known allergy, pneumothorax, pulmonary hemorrhage)

3. Known or suspected pregnancy
4. Stage 4 severe chronic kidney disease or requiring dialysis (i.e., eGFR < 30)
5. Liver failure (Child-Pugh Class C)
6. Anticipated transfer to another hospital, which is not a study site within 72 hours
7. Current participation or participation in another study within the last month that in the opinion of the investigator would prevent enrollment for safety purposes
8. Consent declined

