#### Closed suction tracheal aspirate samples

TA samples will be taken at 0, 8, 16, 24, 48 and 72 hours. The t=0-hour sample will additionally provide an estimate of baseline surfactant composition and concentration. The subsequent samples will be used for the mechanistic studies outlined above (section 2) and will assess the efficacy of surfactant administration. Baseline TA samples will be collected immediately before administration of the first dose of surfactant (t=0h). Samples will then be collected immediately before the second (t=8h) and third (t=24h) doses of surfactant and at 16, 48 and 72 hours thereafter if the patient is still intubated.

Additional TA samples will be taken for diagnostic PCR for SARS-CoV-2 on Days 3 (72 hrs), 5, 10, 15 and 28 (if still hospitalised).

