### 7.8 Long term follow-up assessments

Patients will be monitored constantly as part of their routine clinical care in the intensive care unit. For the purpose of the study, follow up data will be recorded hourly from the administration of the last dose

of surfactant (24 hours) until 32 hours post first dose, 4 hourly until 48 hours post first dose and then daily until day 28, or until the time that the patient is discharged from hospital if this takes place first. A chest ultrasound will be performed daily until this time.

There is no anticipated risk of losing patients to follow up given that they will be hospitalised. Patients may choose to withdraw from the study when they re-gain the capacity to consent for themselves. In these cases, no additional data will be collected. Data can be collected retrospectively by the research team as intensive care records will remain available.

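### The primary test omits patients who die before the endpoint, and the conditional worst-rank fallback does not separate death from extubation alive, which matters for the Ventilation Index

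*Protocol*

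**What the plan says.** Protocol section 10, Efficacy, plans a model-based multiple contrast test of change from baseline, separately for PaO2/FiO2 and VI, 24 h after the last dose. The last dose is planned at 24 h, so this is the 48 h co-primary time point of section 3.3.1.

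The analysis set is fixed there: "The primary analysis will be done on patients with observed data at 24 hours", labelled completers. Sensitivity analyses follow only "if data are missing at 24 hours in an informative manner (e.g., due to death"), and for these "a non-parametric approach can accommodate missing data by assigning the worst rank". No other reason for missingness is named, and extubation does not appear in section 10.

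Four other places bear on the point:
- Section 3.1 defines VI from respiratory rate, peak inspiratory pressure, PEEP and PaCO2.
- Section 6.2 excludes "Imminent expected death within 24 hours"; the endpoint lies at 48 h.
- Section 7.7 makes later tracheal aspirates conditional: "at 16, 48 and 72 hours thereafter if the patient is still intubated".
- Section 7.8 states: "There is no anticipated risk of losing patients to follow up given that they will be hospitalised".

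**The concern.** Two kinds of patient can lack a 48 h value for opposite reasons.

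The first dies. The participants are ventilated patients with severe COVID-19, and the exclusion covers only death expected within 24 h. Section 7.8 dismisses loss to follow-up because patients are in hospital, which does not deal with death. Dropping a death from its arm breaks the as-randomised comparison and flatters whichever arm loses its sickest patients. With three treated patients per cohort, one loss is a third of a dose level.

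The second is extubated alive. VI needs ventilator pressures, so it cannot be measured, and the reason is plainly informative. Read as worded, the fallback treats this patient like one who died. That would contradict the protocol's own ordering in section 3.3.2, where leaving invasive ventilation moves a patient off category 6 in the good direction, death alone is category 7, and ventilator-free days count as benefit.

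At stake is an efficacy signal meant to inform a larger trial: the primary test may err one way and its fallback the other.

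**Working it through.** **The plan's own figure.** The power table (12 controls, four cohorts of 3) makes no mention of missing values. A simulated contrast test with complete data reproduces all 12 rows within 2 points, for example 0.89 and 0.82 at CV 20%. The settings are log scale, one-sided 5%, linear and Emax contrasts, and an assumed Emax ED50 of 20 vials; the last three of these are partly or wholly assumptions, because the protocol states neither sidedness nor ED50. The table is therefore matched with no allowance for deaths or extubations. The calculations below use the 12 treated and 8 controls of section 4.

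**Inputs.** CV 20% is the more favourable of the two values in the table. On the log scale SD = sqrt(ln(1 + 0.20²)) = sqrt(ln 1.04) = 0.198. The protocol gives no death or extubation rate, so counts of 0 to 3 are assumed. Outcomes are coded so that higher is better.

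**1. Completers, losses in the treated arm only, no drug effect.** Take 12 draws from N(0, 0.198), drop the lowest k and average the rest:

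| Lowest k of 12 dropped | Mean of the rest (log) | As % |
|---|---|---|
| 1 | +0.029 | +3.0% |
| 2 | +0.054 | +5.6% |
| 3 | +0.078 | +8.1% |

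In a simulated one-sided 5% t-test of 12 v 8 (20,000 runs), false positives go from 0.047 with no loss to 0.107 with one and 0.169 with two treated deaths dropped.

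**2. Completers, similar proportions lost in both arms.** Drop the lowest 3 of 12 treated and the lowest 2 of 8 controls, 25% of each:
- treated shift +0.078, control shift +0.075
- difference 0.078 − 0.075 = 0.003 log units, about 0.3%

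With one death in each arm (1 of 12 and 1 of 8) the simulated estimate is −1.2% and the false-positive rate 0.052. The bias therefore comes from imbalance between the arms, and its direction depends on which arm loses more.

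**3. Rank fallback, extubations in the treated arm only, true benefit 25%.** One-sided Wilcoxon test, 12 v 8; extubated patients are assumed to be those with the highest values:

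| Treated patients extubated | Power, scored worst | Power, scored best |
|---|---|---|
| 0 | 0.74 | 0.74 |
| 1 | 0.46 | 0.74 |
| 2 | 0.17 | 0.74 |
| 3 | 0.02 | 0.76 |

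This is a two-group stand-in for the planned contrast test. It applies to VI only.

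Blocks 1 and 3 are upper-end cases, because the extreme values are the ones removed or rescored and all losses fall in one arm.

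**The case against.** The protocol already commits to a worst-rank analysis when deaths cause missing values, so part of the dispute is which analysis is called primary. Deaths also stay visible elsewhere: 28-day mortality and serious adverse events are endpoints, safety is reviewed after each cohort, and section 10 reports the proportion of participants with efficacy data. The trial is an exploratory pilot of up to 20 patients. All of this stands and limits the weight of the point. It does not change the fact that the named primary result excludes deaths.

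Several stronger readings are tempting but not supported:
- **That the protocol orders extubated patients to be ranked worst.** It does not. It says a rank approach can be used and names only death, so a narrow reading confines the worst rank to deaths, and an analysis plan not shown may settle this. What holds is that the wording does not separate the two cases.
- **That both co-primaries are hit equally.** Only VI needs ventilator pressures. Section 7.7 lists PaO2 and FiO2 among values recorded to 48 h, although its arterial gas sampling times end at 36 h.
- **That the result will be biased by 3% to 8%.** Those figures assume losses only among treated patients and only the lowest values. Proportionate losses nearly cancel.
- **That the shift can be measured against the 20% efficacy threshold.** That threshold belongs to the interim Bayesian rule, for which no completer rule is stated.
- **That the aspirate condition shows how often extubation occurs.** It shows only that extubation by those times is foreseen.

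Replacing the primary model with ranks would also have a price: section 10 adjusts the model for baseline and uses its fits to estimate doses.

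**Conclusion.** The point holds as a matter of wording and analysis choice. The primary test leaves out patients who die before the 48 h value, the only analysis that counts them is conditional, and its worst-rank rule does not distinguish death from extubation alive. The extubation part is firm for VI only and depends on reading the informative-missingness wording broadly, which the text permits but does not require.

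No size can be stated for this trial, because the protocol gives no death or extubation rate. The 3.0%, 5.6% and 8.1% shifts illustrate 1, 2 or 3 losses confined to the treated arm; balanced losses bring the bias close to zero. With 12 treated and 8 controls, an imbalance of one or two patients is enough to matter, so the handling should be fixed in advance. The change is worth making but does not invalidate the design.

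**What to change.** 1. Run a rank-based analysis of all randomised patients at the primary time point in every case, not only when missingness is judged informative, and report it beside the completer contrast test.
2. Score by reason. Death before the time point takes the worst rank. Extubated and alive takes the best rank for VI. PaO2/FiO2 uses the measured gas where one is available. Other missing values are handled separately.
3. The sponsor should define in advance where a patient on ECMO is ranked.
4. Keep the model-based completer analysis for effect size and dose estimation, and do not claim efficacy from it if the all-randomised rank analysis points the other way.

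The cost is a change of wording in section 10 and some extra analysis. The model and its power table can stay as they are on this point. The downside is a possibly less favourable result if deaths fall mainly in the treated arm.
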